### 2.5. Protocol

This study follows a standardized protocol to ensure consistency in participant recruitment, intervention delivery, and outcome assessment across multiple study sites. The study protocol consists of four key phases: screening and enrollment, baseline assessment, intervention, and post-intervention assessment.

Participants will be recruited from outpatient rehabilitation programs at participating institutions. Eligibility will be determined through a pre-screening process based on inclusion and exclusion criteria. Those who meet the eligibility criteria will proceed to the informed consent process, where they will receive detailed explanations regarding the study’s objectives, procedures, potential risks, and expected benefits.

After enrollment, all participants will undergo a comprehensive baseline assessment, which includes collecting demographic and clinical data such as age, sex, stroke history, and comorbidities. Functional assessments will be conducted to evaluate muscle strength, physical performance, body composition, and cardiopulmonary fitness. These baseline evaluations will establish pre-intervention values for subsequent comparisons.

Following randomization, the intervention group will participate in an 8-week high-speed power training (HSPT) program conducted twice per week, with each session lasting 60 min. The exercise protocol will include a 10 min warm-up, a 40 min main training session focused on progressive resistance exercises emphasizing power development, and a 10 min cool-down incorporating stretching and relaxation techniques. In contrast, the control group will continue their daily routine without participating in structured resistance training while still receiving standard medical care.

Upon completing the 8-week program, all participants will undergo a post-intervention assessment identical to the baseline evaluation. This assessment will measure changes in muscle strength, gait speed, balance, body composition, and cardiopulmonary fitness to determine the effects of the intervention.

This protocol ensures a structured and reproducible methodology for intervention implementation and data collection, thereby enhancing the reliability and validity of study findings across multiple sites.

### 2.6. Intervention Program

The intervention program is based on the principles of HSPT and aims to improve muscle strength, power, and functional mobility in stroke survivors with sarcopenia. Structured training is conducted twice per week for 8 weeks, with each session lasting 60 min and consisting of three sequential phases: warm-up, main exercise, and cool-down. The detailed composition of the program is presented in Table 1.

The warm-up phase (10 min) includes aerobic walking and static or dynamic stretching to increase body temperature, enhance circulation, and prepare joints and muscles for high-velocity movements.

The main exercise phase (40 min) consists of resistance training targeting the lower body, trunk, and upper body, using TheraBand (Hygenic Corporation, Akron, OH, USA) as the primary resistance tool. Exercises are performed according to a high-speed power training protocol characterized by an explosive concentric contraction, followed by a brief 1 s pause, and then a controlled eccentric contraction lasting more than 2 s. This sequence is designed to activate fast-twitch muscle fibers, which are often compromised in stroke survivors, and to improve rapid force production essential for functional tasks such as gait, sit-to-stand transfers, and balance recovery.

The exercise selection includes squats, lunges, and bridges for the lower body; leg raises, reverse crunches, sit-ups, back extensions, and deadlifts for the trunk; and chest presses, back rows, shoulder presses, biceps curls, and triceps extensions for the upper body. The intensity and resistance are progressively increased based on individual capability, with modifications made in accordance with the principles of progressive overload and task specificity. Exercise specialists closely monitor performance to ensure proper technique and safety throughout the program.

The cool-down phase (5 min) consists of light walking and flexibility exercises, aimed at promoting active recovery, reducing muscle soreness, and improving joint range of motion.

This training program is standardized across all participating study sites and delivered by experienced exercise professionals specializing in stroke rehabilitation. The protocol is individualized according to each participant’s physical condition and recovery status, integrating principles of safety, adaptability, and progression. By combining resistance training with speed-focused contraction patterns, the program is expected to enhance functional outcomes and support the community reintegration of stroke survivors with sarcopenia.

### 2.7. Outcome Measures

All participants will complete a comprehensive evaluation twice during the study: once prior to the intervention (baseline) and once again after the completion of 16 training sessions (post-intervention). Evaluations will be conducted by trained assessors who are blinded to group assignments. In addition to clinical and demographic characteristics, a range of physical health and function indicators will be measured to assess the effects of the intervention. These characteristics are summarized in Table 2.

#### 2.7.1. Muscle Strength

Muscle strength will be assessed using both grip strength and isokinetic muscle strength testing [26,27]. Grip strength will be measured using a hand dynamometer (TKK-5401; Takei Scientific Instruments, Tokyo, Japan), which provides a reliable index of general upper limb strength. It is also widely used as a proxy for overall muscle function and sarcopenia screening. For the lower limbs, isokinetic testing will be conducted using the Humac Norm system (CSMi, Stoughton, MA, USA) to quantify peak torque and muscle endurance at preset angular velocities. This method allows for the objective evaluation of dynamic strength in the major muscle groups, particularly in the knee extensors and flexors, which are critical for postural control and mobility in stroke survivors.

#### 2.7.2. Body Composition

Body composition will be evaluated using dual-energy X-ray absorptiometry (DXA) with Discovery Wi (Hologic, Waltham, MA, USA) and bioelectrical impedance analysis (BIA) with InBody S10 (InBody, Seoul, Republic of Korea). DXA will be used to provide accurate measurements of whole-body lean mass, appendicular skeletal muscle mass, and body fat percentage. In addition, BIA will be employed to assess segmental lean mass and fat distribution. From these data, the skeletal muscle mass index (SMI) will be calculated as appendicular lean mass divided by height squared (kg/m^2^), which is a key diagnostic criterion for sarcopenia. These complementary methods offer a comprehensive view of changes in body composition resulting from the training program.

#### 2.7.3. Physical Performance

To assess physical performance, the short physical performance battery (SPPB) will be administered. This tool includes a timed gait speed test, repeated chair stands, and static balance tasks, collectively providing an index of lower extremity function. The SPPB is a validated instrument commonly used in geriatric and rehabilitation populations to quantify mobility and functional impairment [28].

#### 2.7.4. Balance and Gait

Both static and dynamic balance, as well as gait function, will be evaluated. The Berg Balance Scale (BBS) will be used to measure static balance across 14 functional tasks, with higher scores indicating better balance ability [29]. To assess dynamic balance and mobility, the timed up and go (TUG) test will be administered [30]. This test measures the time it takes for a participant to rise from a chair, walk three meters, turn around, walk back, and sit down again. In addition, the 10 m walk test (10MWT) will be used to assess usual gait speed over a short distance, an important predictor of community ambulation potential and functional independence in stroke survivors [31].

### 2.8. Participant Timeline

All participants will follow a structured timeline that includes screening, the baseline assessment, the intervention phase, and the post-intervention assessment. Initially, eligible participants will be recruited from outpatient rehabilitation centers at four participating institutions. A preliminary screening process will be conducted to confirm eligibility based on the study’s inclusion and exclusion criteria, and written informed consent will be obtained prior to enrollment.

Following consent, participants will complete a baseline evaluation prior to randomization. This assessment will include the collection of demographic and clinical information, as well as a comprehensive set of physical function measures such as muscle strength, body composition, physical performance, and balance. The assessment tools used for each domain are detailed in Table 2 and Table 3.

Following randomization, 120 participants will be allocated to either the intervention or control group. As previously detailed, the intervention group will complete an 8-week high-speed power training program, while the control group will continue their usual activities with general health education. This section serves to summarize the overall study timeline, consolidating key steps such as recruitment, baseline assessment, intervention, and post-intervention evaluation. This repeated measurement design will enable pre–post-comparisons to evaluate the effects of the training program on physical function and body composition in stroke survivors with sarcopenia. All procedures will be standardized across sites to ensure consistency in delivery and data collection, and the study timeline will be structured in accordance with the SPIRIT guidelines [25].

### 2.9. Statistical Analysis

The statistical analysis for this study will be conducted using IBM SPSS Statistics (version 26.0; IBM Corp., Armonk, NY, USA). Before the trial, a sample size calculation was performed using G*Power (version 3.1.2), assuming an effect size of 0.5, a significance level (α) of 0.05, and a statistical power of 80% (1–β). The effect size (Cohen’s d = 0.5) was selected based on prior studies showing the moderate-to-large effects of high-velocity or multicomponent resistance training in stroke or sarcopenic populations [19,20]. An anticipated attrition rate of 20% was assumed, consistent with previous 8–12-week intervention studies in community-dwelling stroke survivors [21], resulting in an adjusted target of 120 participants. Based on these assumptions and accounting for possible attrition, a total of 120 participants will be recruited—30 individuals from each of the four participating institutions.

Descriptive statistics will be computed to characterize the participants and evaluate baseline equivalence between the intervention and control groups. Categorical data will be presented as frequencies and percentages, while continuous data will be summarized as means with standard deviations or medians with interquartile ranges, depending on the distribution. To assess baseline group differences, independent *t*-tests or Mann–Whitney U tests will be used for continuous variables, and chi-square tests or Fisher’s exact tests will be applied for categorical variables.

The analysis will adhere to an intention-to-treat (ITT) principle. The normality of the outcome variables will be evaluated using the Shapiro–Wilk test. Depending on the distribution, either parametric or non-parametric tests will be selected accordingly. To examine intervention effects, two-way repeated-measures ANOVA will be employed with group (intervention vs. control) as the between-subject factor and time (pre- and post-intervention) as the within-subject factor. Interaction effects will be interpreted to determine the differential change over time between groups. Where sphericity assumptions are violated, appropriate corrections (e.g., Greenhouse–Geisser adjustment) will be applied.

All hypothesis testing will use a two-sided α level of 0.05. Estimates of intervention effect will be accompanied by 95% confidence intervals.

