### 2.2. Study Design

This study will be conducted across four medical and rehabilitation centers and follow a randomized, double-blind, parallel-group design to assess the impact of a community-based resistance training program for stroke survivors with sarcopenia. A total of 120 participants will be randomly assigned in a 1:1 ratio to either the intervention group, which will engage in structured resistance training, or the control group, which will continue their routine activities without a structured exercise program. To ensure unbiased results, assessors conducting evaluations will remain blinded to group assignments throughout the study.

The study will be conducted at (1) the National Rehabilitation Center, (2) Bucheon SM Hospital, (3) Korea University Anam Hospital, and (4) the National Health Insurance Service Ilsan Hospital. Participants will be recruited from outpatient rehabilitation programs at these institutions. Eligibility will be confirmed through a pre-screening process, followed by an informed consent procedure to ensure that participants fully understand the study objectives and methodology.

Once enrolled, participants will undergo baseline assessments before randomization. The intervention group will participate in a high-speed power training program designed to enhance muscle strength, functional performance, and mobility. The program will be conducted twice a week for 8 weeks, with each session lasting 60 min and incorporating progressive resistance exercises. Meanwhile, the control group will maintain their regular daily activities without any structured exercise intervention while continuing to receive standard medical care.

Outcome assessments will be conducted at two key time points: before the intervention (baseline) and after completing the 8-week program (post-intervention). The overall study procedure, including recruitment, group allocation, intervention, and assessments, is illustrated in Figure 1. The outcome measures will include muscle strength, physical function, body composition, and cardiopulmonary fitness. The collected data will undergo statistical analysis to evaluate the effectiveness of the resistance training program in mitigating sarcopenia-related functional decline among stroke survivors.

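### The stated 80% power does not follow from the plan's own inputs: for d = 0.5 in the tested quantity, 120 randomised with 20% attrition gives about 68%

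*Protocol article*

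**What the plan says.** All the inputs are in the protocol article.

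- Section 2.9 gives the calculation as "assuming an effect size of 0.5, a significance level (α) of 0.05, and a statistical power of 80% (1–β") and identifies the effect-size measure: "The effect size (Cohen’s d = 0.5) was selected based on prior studies".
- On dropout it says "An anticipated attrition rate of 20% was assumed", "resulting in an adjusted target of 120 participants".
- On sidedness it says "All hypothesis testing will use a two-sided α level of 0.05".
- Section 2.2 gives the allocation: "A total of 120 participants will be randomly assigned in a 1:1 ratio".
- The analysis in section 2.9 is a "two-way repeated-measures ANOVA will be employed with group (intervention vs. control) as the between-subject factor" and time (pre and post) as the within-subject factor. The treatment effect is read from the interaction: "Interaction effects will be interpreted to determine the differential change over time between groups".

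The article does not give the sample size before the attrition allowance, the G*Power test that was chosen, the outcome to which d refers, or a pre-post correlation.

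**The concern.** For a two-group comparison at d = 0.5, two-sided 0.05 and 80% power, the familiar requirement is 64 per arm. That total of 128 already exceeds 120, although 120 is presented as the figure after inflation for dropout. No method of allowing for attrition can bring a number down, so on this reading the stated inputs and the stated result cannot all be right.

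The stated power is the reader's basis for interpreting a null result. At 80% power, a true effect of the planned size is missed one time in five. At 68% it is missed about one time in three, and a non-significant result would be given more weight than it deserves.

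**Working it through.** **Inputs.** d = 0.5, alpha = 0.05 two-sided, target power 80%, attrition 20% (all section 2.9); 1:1 allocation of 120, so 60 per arm (section 2.2).

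**Which test.** With two time points, the group-by-time interaction in a repeated-measures ANOVA is equivalent to a two-sample t-test on the change scores. The two-sample noncentral t calculation therefore applies directly when d is the standardised difference in change.

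**Step 1: try to reproduce 120.** Noncentrality is δ = d·√(n/2) with 2n − 2 degrees of freedom, for n per arm.

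- n = 63: power 79.5%.
- n = 64: δ = 0.5·√32 = 2.83, power 80.1%.

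So 64 per arm, or 128 evaluable, are needed. After attrition, 128/0.8 = 160 randomised. The stated 120 is not reproduced.

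**Step 2: power that 120 gives.**

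| Evaluable | Per arm | δ at d = 0.5 | Power |
|---|---|---|---|
| 120 × 0.8 = 96 | 48 | 0.5·√24 = 2.45 | 67.9% |
| 120 (no attrition) | 60 | 0.5·√30 = 2.74 | 77.5% |

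**Step 3: detectable effect.** With 48 per arm, power reaches 80% at d = 0.578, or about 0.58.

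**Step 4: d on the raw outcome SD.** If d = 0.5 is scaled to the SD of the outcome at one time point, and the SD is equal at both times, the change score has SD √(2(1 − ρ)) times as large. The effective d for the interaction is then 0.5/√(2(1 − ρ)). A baseline-adjusted ANCOVA has effective d of approximately 0.5/√(1 − ρ²). The article gives no ρ, so the values below are assumptions that show the range, at 48 per arm.

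| Assumed ρ | Planned interaction test | ANCOVA (not planned) |
|---|---|---|
| 0.3 | 54% | 72% |
| 0.4 | 60% | 75% |
| 0.5 | 68% | 79.9% |
| 0.6 | 77% | 86% |
| 0.63 | about 80% | 88% |
| 0.7 | 88% | 92% |

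**Step 5: repeated-measures settings in G*Power.** For two groups, d = 0.5 corresponds to f = 0.25.

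- *Between factors*, two measurements: λ = N·f²·2/(1 + ρ). At ρ = 0.5, N = 98 and 98/0.8 = 122.5; power at 96 is 79.9%. At ρ = 0.48, N = 96 and 96/0.8 = 120.
- *Within-between interaction*, two measurements: λ = N·f²·2/(1 − ρ). At ρ = 0.5, N = 34 and 34/0.8 = 42.5, so 43. This is far from 120.

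The between-factors setting comes close to or meets 120, but it tests the group difference averaged over baseline and follow-up. The analysis in section 2.9 is read from the interaction.

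**The case against.** The strongest reply is that the 68% is conditional. Section 2.9 does not name the test used in G*Power, and the planned analysis is a repeated-measures one. If d is on the raw SD and the pre-post correlation is above about 0.63, the planned interaction test has at least 80% power with 96 evaluable participants. This stands. A reader might infer that the trial is certainly underpowered, and the documents do not support that: without a correlation, true power on the raw-SD reading could lie on either side of 80%. What can be said is that the stated 80% does not follow from the stated inputs.

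A second reply is that a two-sided repeated-measures route does lead to about 120 with the correct division by 0.8, namely the between-factors calculation with a correlation of 0.48 to 0.5. The arithmetic is right, but it does not rescue the statement. It powers the group main effect, not the interaction. Under randomisation the expected baseline difference is zero, so a difference of 0.5 averaged over both times would require a difference twice as large at follow-up. It also needs a correlation that the article does not give.

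This route also rules out another tempting inference. A one-sided normal approximation gives 50 per arm, and 100 × 1.2 = 120, so a reader might conclude that a one-sided test was used and attrition was added by multiplication. Nothing in the article says either, section 2.9 specifies two-sided testing, and another route reaches the same number.

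A third reply is that a condensed article may leave the test family, the unadjusted N and the correlation to a fuller document. That is fair for those items taken alone, and their absence is not the point here. The article does state the effect size, alpha, sidedness, power, attrition and result, and these disagree. The planned 95% confidence intervals will help readers of a null result, but they do not correct the power statement.

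**Conclusion.** The point holds in this form: the 80% power stated in section 2.9 cannot be obtained from the inputs stated there for the test planned there. With d = 0.5 as the standardised difference in the change score, two-sided 0.05 and 20% attrition, 120 randomised gives about 68% power. The shortfall is 32 evaluable participants (128 − 96), or 40 randomised (160 − 120); equivalently, the detectable effect at 80% power is about 0.58 rather than 0.5.

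This rests on d being standardised to the tested quantity. On the raw-SD reading, power ranges from 54% to 88% as the correlation goes from 0.3 to 0.7, and the plan states nothing that would select a value. How 120 was actually obtained cannot be determined from the article. The correction is needed because the sample-size statement is wrong as written and readers will rely on it.

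**What to change.** Keep 120 and rewrite the sample-size paragraph of section 2.9 in one of two ways.

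1. Restate what 120 gives: *120 randomised, 96 expected evaluable; about 68% power for d = 0.5 and 80% power for d = 0.58 (two-sided 0.05), where d is the between-group difference in change divided by the SD of change.*
2. Specify a baseline-adjusted ANCOVA as the analysis of the treatment effect, define d on the raw outcome SD, and state the assumed pre-post correlation with its basis. A correlation of about 0.5 gives about 80% power with 96 evaluable participants.

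In either case, name the test used in the calculation, so that the power statement and the analysis refer to the same effect.

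The first option costs one paragraph and a less favourable power figure. The second also replaces the repeated-measures ANOVA in the analysis text, which should be done before any outcome data are seen by group. Neither needs more participants. Holding to 80% power for d = 0.5 in the change score would instead need 160 randomised.

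### A normality pre-test on the raw outcomes selects the efficacy test while the next sentence fixes it as repeated-measures ANOVA, so neither test nor estimand is settled

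*Protocol article*

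**What the plan says.** All of this is in section 2.9 (Statistical Analysis) of the protocol article unless noted.

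- Pre-test: "The normality of the outcome variables will be evaluated using the Shapiro–Wilk test". No test level is given, nor whether normality is judged per arm, per visit, pooled, on change or on residuals.
- Selection rule, immediately after: "Depending on the distribution, either parametric or non-parametric tests will be selected accordingly".
- Efficacy analysis, immediately after that and with no condition attached: "To examine intervention effects, two-way repeated-measures ANOVA will be employed with group (intervention vs. control) as the between-subject factor". Time is the within-subject factor.
- Effect of interest: "Interaction effects will be interpreted to determine the differential change over time between groups".
- Mann–Whitney U is named only for comparing the arms at baseline: "To assess baseline group differences, independent *t*-tests or Mann–Whitney U tests will be used for continuous variables".
- Reporting: "Estimates of intervention effect will be accompanied by 95% confidence intervals".

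Section 2.2 sets two assessments, at baseline and after the 8-week programme. Sections 2.3 and 2.4 stratify randomization by site and baseline functional status. Section 2.4 also blinds the data analysts.

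**The concern.** The selection rule and the ANOVA sentence answer the same question differently. If the ANOVA is used whatever the data look like, the pre-test has no role in the efficacy analysis. If the pre-test decides, the ANOVA is only one of two branches. A reader cannot tell from the text which test will be reported for a given outcome.

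The choice changes what is estimated. The interaction estimates a difference in mean change. A rank test on change concerns a shift in the distribution of change, and a rank test on post scores concerns post scores. Because the pre-test is run outcome by outcome, grip strength, SPPB, BBS and TUG could end with different estimands in one trial. Which one each gets would depend on sampling variation, scale granularity and ceiling effects.

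The rule also tests the raw outcome variables, which is not what the stated analysis needs to be close to normal.

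**Working it through.** **1. Which quantity the analysis depends on.** Write D = post − baseline for each participant. With two visits, the group-by-time F statistic equals the square of the two-sample t statistic on D. Its normality assumption therefore concerns D within arm, that is, the residuals. A raw score can be skewed while D is not, and the reverse. With two levels of time, sphericity cannot fail either, so the correction mentioned in section 2.9 does not bear on this.

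**2. Inputs.** From the documents: 120 participants randomized 1:1, so 60 per arm; 20% attrition, so 60 × 0.8 = 48 per arm; two-sided α = 0.05; d = 0.5. Not in the documents, hence assumed: the outcome distributions and the pre–post correlation. The plan attaches no figure to the pre-test rule, so there is none to reproduce.

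**3. How often Shapiro–Wilk (5% level) rejects in one sample of 48.** Simulated, 3,000 samples per shape:

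| Assumed shape | Rejection |
|---|---|
| Normal outcome | 5% |
| BBS, rounded, range 0–56, SD 8, mean 40 / 45 / 48 | 5% / 39% / 89% |
| SPPB, rounded, range 0–12, SD 2.5, mean 7 / 8 / 9 | 21% / 44% / 92% |
| TUG, log-normal, CV 0.3 / 0.5 / 0.7 | 53% / 89% / 98% |
| SPPB change, rounded, SD 1.5 / 1 | 77% / 100% |

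The unit of testing also matters. If any of the four arm-by-visit cells can trigger the switch, treating them as independent gives 1 − 0.95⁴ = 19% for truly normal data (17–18% simulated with correlated visits).

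**4. What the switch does.** Simulated at 48 per arm, assumed correlation 0.7, shift 0.5 SD, any-cell trigger. Shapes: normal; SPPB mean 7.5, SD 2.5; BBS mean 45, SD 8; TUG log-normal.

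- Interaction test (t-test on change): power 83–88%.
- Mann–Whitney on change: 81–87%.
- Mann–Whitney on post scores: 63–66%.
- Two-stage rule that switches to post scores: 84% (normal), 66% (SPPB), 66% (BBS), 65% (TUG).
- Type I error of that two-stage rule with the fallback fixed in advance: 5.0–5.3%.
- Type I error if the smallest p among the three tests is reported: 10.0–10.5%.

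A repeat with a different random seed agreed to within about 2 percentage points.

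**5. One pre-specified analysis instead.** Normal approximation, post-score SD = 1, correlation r:

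power = Φ(0.5 × √(48/2) / s − 1.96), where 0.5 × √24 = 2.449, s = √(2(1 − r)) for the interaction, s = √(1 − r²) for ANCOVA and s = 1 for post scores.

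| r | s, interaction | Power | s, ANCOVA | Power |
|---|---|---|---|---|
| 0.3 | 1.183 | Φ(2.070 − 1.96) = 54% | 0.954 | Φ(2.568 − 1.96) = 73% |
| 0.5 | 1.000 | Φ(2.449 − 1.96) = 69% | 0.866 | Φ(2.828 − 1.96) = 81% |
| 0.7 | 0.775 | Φ(3.162 − 1.96) = 88% | 0.714 | Φ(3.430 − 1.96) = 93% |

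Post scores alone give Φ(2.449 − 1.96) = 69% at every r. They lose to the interaction only when r exceeds 0.5. The ANCOVA column credits baseline adjustment only; any gain from the strata is not counted.

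**The case against.** The strongest reply is that this is a condensed article and an unseen analysis plan may name the rank test. That stands as far as the missing name goes, and the missing name is not the point here. The selection rule and the unconditional ANOVA sentence are both printed in section 2.9, and naming a fallback elsewhere would not reconcile them or move the pre-test onto the right quantity.

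Several stronger readings are tempting, and the documents do not support them.

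- *The scales will usually fail the test.* No mean, SD or shape is given for any outcome. The simulated shapes cover three of the eight tools in Table 3, and rejection can be as low as 5%. What can be said is that the switch may fire for some outcomes and not for others.
- *A switch necessarily loses precision or discards baseline.* A rank test on change uses baseline by subtraction and loses little power. For log-normal TUG with CV 0.5 or more it can gain: with a multiplicative effect of 0.35 log-SD and correlations of 0.5–0.85, 35–80% against 33–76% at CV 0.5.
- *A switch gives up the strata.* The ANOVA as described has only group and time, so it does not use them either.
- *A switch breaks a promised mean-difference interval.* Section 2.9 promises intervals for effect estimates without specifying a mean difference. A Hodges–Lehmann shift with its interval would meet that wording.
- *The pre-test inflates false positives.* With a fallback fixed in advance it does not.

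Analyst blinding (section 2.4) is a genuine mitigation. It makes it hard to favour a direction. It does not prevent preferring the smaller p-value, and it does not settle the estimand.

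**Conclusion.** The concern holds in a limited form. Section 2.9 does not fix the efficacy test: a data-driven selector is followed by an unconditional commitment to one test, and the selector looks at raw outcomes when the stated interaction depends on change.

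The size depends on what the unnamed branch would be. It is negligible for a rank test on change. For post scores, power falls from about 83–88% to about 65% at an assumed correlation of 0.7, with no loss at 0.5 or below under the normal approximation. Type I error stays near 5% under a fixed rule and reaches about 10% only if the test is picked by its p-value. All these figures rest on assumed distributions and correlations, on d = 0.5 and on 48 per arm.

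This is worth correcting because a better analysis is available from data already collected, and not because the present rule is shown to invalidate the trial.

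**What to change.** In section 2.9, and in the analysis plan if there is one:

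1. Remove the normality test as the selector of efficacy tests.
2. Name one between-arm analysis for each outcome: ANCOVA of the post-intervention value adjusted for baseline, site and functional stratum.
3. State how the 95% confidence interval is obtained (heteroscedasticity-robust or bootstrap).
4. Inspect residuals descriptively, with no switch attached.
5. Name one rank-based analysis, as a sensitivity analysis only.
6. A transformation, such as log TUG, is optional. If used, fix it in advance and say that the effect is then a ratio.

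If the sponsor prefers to keep the group-by-time interaction, making it unconditional would remove the contradiction, at the lower power shown above.

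The cost is analysis wording only: no extra participants, visits or measurements.
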